#### Tools

Participants will be asked to complete an appropriate questionnaire to identify self-reported sociodemographic characteristics (age, salary band, position in the company, highest level of education and smoking status), sedentary behaviour, diet and beverage consumption, mental health and absenteeism.

Self-reported sedentary behaviour in the previous 7 days will be quantified using the Last 7 Days Sedentary Time Questionnaire (SIT-Q-7d). The questionnaire includes self-reported sedentary time in five main domains as well as sleep and nap time. The domains include sedentary time during meals, travel, work, recreation and during other non-specified sedentary time. The SIT-Q-7d is acceptable for use in epidemiological studies, with criterion validity for domain-specific variables ranging from 0.22 to 0.76 (Wijndaele et al. 2014).

Habitual consumption of vegetables, fruit, whole grains, dairy, meats and poultry over the past year will be determined using a self-reported dietary intake questionnaire (Kolbe-Alexander et al. 2008). A beverage intake questionnaire (BEVQ-15) quantifies the amount of unsweetened beverages, sugar-sweetened beverages and alcohol consumed by the participants, with validity between 24-h food item recall and BEVQ-15 ranging from rho values of 0.69 to 0.76 (*p* < 0.001) (Hedrick et al. 2012). The estimated number of kilocalories per drink will be calculated.

The Centre for Epidemiological Studies Depression Scale (CES-D-10) is a validated questionnaire (rho = 0.81–0.94, *p* < 0.05 [Baron, Davies & Lund 2017]) that estimates the mental health status of employees, specifically eliciting symptoms of depression in the past 7 days (Andresen et al. 1994). The tool includes items on the effect of depression, somatic symptoms and positive effects. A four-point Likert scale is used for each item, ranging from ‘rarely or none of the time’ to ‘all of the time’.

#### Cardiorespiratory fitness

The Queens College 3-min step test will be used to estimate cardiorespiratory fitness (using maximal oxygen uptake [VO_2max_]). The agreement between this step test and measured VO_2max_ is high (rho = 0.75, *p* < 0.001). The step test uses a 41.3-cm step with a stepping rate of 24 steps/min for men and 22 steps/min for women for a period of 3 min (American College of Sports Medicine 2017). Within 5 s of the participant sitting, a research assistant will measure the post-exercise heart rate (HR). Maximal oxygen uptake (VO_2max_) will be calculated for men (VO_2max_ = 111.33 – [0.42 × HR]) and women (VO_2max_= 65.81 – [0.1847 × HR]).

### Phase 2

All study participants involved in the combined standing desk–healthy messages intervention and who did not drop out of the RCT will be invited to participate in semi-structured focus groups at intervention follow-up to evaluate their perceptions of the intervention – receiving the healthy messages and/or using the standing desks – and their perceptions of the effectiveness of using these interventions in the workplace. Six focus groups are planned, with six to eight participants per group. Given that this intervention group will have approximately 60 participants, and that not all participants will make themselves available for a focus group, the intention to invite all intervention group participants to take part in a focus group accounts for at least a 60% positive response rate. Although the challenges associated with recruitment for focus groups can sometimes make it difficult to stratify focus groups, an attempt will be made to stratify these focus groups based on participants’ responses to phase 1. During the focus group discussions, participants will be asked to comment to facilitators and address extended sitting time whilst working, and to discuss the most suitable methods to improve health in their place of work. The focus groups will be approximately 45 – 60 min in duration.

For this qualitative component of the project, the following ‘big-tent’ criteria of qualitative quality will be considered and applied: a worthy topic, rich rigour, sincerity, credibility, resonance, significant contribution, ethical and meaningful coherence (Tracy & Hinrichs 2017). At this stage of the study, it can be argued that this study addresses a worthy topic (the prevention of non-communicable diseases (NCDs) in an LMIC) and could make a significant contribution to the literature on this topic in South Africa. Furthermore, in relation to rich rigour, appropriate sampling, data collection and data analysis methods have been planned; ethical considerations are discussed below. Sincerity, credibility, resonance and meaningful coherence are criteria that are not really possible to apply at this stage of the research, given that this is a protocol paper and does not yet report on study findings. These criteria are particularly relevant for the interpretation of findings and how these findings are presented.

## Data analysis

All data for the RCT will be analysed using Stata Special Edition (SE) (version 14, Stata Corp, United States of America). Descriptive statistics will be used for comparing outcome data at baseline and change from baseline to follow-up between the intervention and control groups. Paired *t*-tests for within-group comparisons over time or their non-parametric equivalents depending on data distribution will be utilised. Comparison between groups will be made using analysis of variance or the non-parametric equivalent. Multivariable linear regression models will be used to determine if any of baseline study variables modulate these effects on the outcome variables (change in BMI, lipids, BP, HbA1c, VO_2max_ and sedentary behaviour). Significance will be accepted at an alpha level of *p* ≤ 0.05. The Consolidated Criteria for Reporting Qualitative Research (COREq) checklist will be used for reporting on the methodology, research team, study design and analysis, and study findings (Tong et al. 2007).

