**Methods/design:**

The protocol will use a mixed-methods study design. Phase 1 of this study is a 12-month, single blinded, randomised controlled trial, which will include baseline, 3-month, 6-month and 12-month post-intervention assessments of plausible cardiometabolic risk biomarkers in office-bound workers at a South African credit and information management company. These biomarkers include anthropometry, sedentary behaviour and physical activity, sleep duration, blood pressure, glucose, glycated haemoglobin (HbA1c), lipid profile and cardiorespiratory fitness. Participants will be randomised into an intervention or control group. The intervention group will be provided with an adjustable sit–stand desk and receive weekly health-promoting messages for the intervention period. Phase 2 will use focus group discussions conducted post-intervention to explore the study participants’ perceptions of the effectiveness of the intervention. Cardiometabolic risk biomarkers and changes in these variables will be compared between the intervention group and the control group at the four time points using descriptive and inferential statistics.

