## Measures

### Phase 1

Data for the RCT will be collected at baseline, 3 months (short term), 6 months (medium term) and 12 months postintervention (long term) using validated measures and standardised assessments.

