#### Blood pressure

The Omron M7 (Intelli IT [HEM-7322T-E], Kyoto, Japan) will be used to record brachial blood pressure (BP). The device has been validated for determining systolic and diastolic BP (El Feghali et al. 2007). Three measurements will be taken after the participant has rested (≥ 5 min) in the seated position with an appropriately sized cuff around the right upper arm, supported at the level of the heart (American College of Sports Medicine 2017). The average of the last two BP measurements will be recorded. Hypertension will be diagnosed as resting systolic BP ≥ 140 mmHg and/or a resting diastolic BP ≥ 90 mmHg, or taking antihypertensive medication. The undiagnosed participants will be advised to seek medical attention.

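### The between-group comparison is planned without adjustment for the outcome's own baseline, and the within-arm paired tests beside it do not test the intervention

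*Protocol article*

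**What the plan says.** The Data analysis section of the protocol article contains four relevant statements.

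- Descriptive statistics serve for "comparing outcome data at baseline and change from baseline to follow-up between the intervention and control groups".
- Paired t-tests are planned "for within-group comparisons over time or their non-parametric equivalents depending on data distribution will be utilised".
- For the arms: "Comparison between groups will be made using analysis of variance or the non-parametric equivalent".
- The role of the baseline variables comes in a further sentence, which reads "Multivariable linear regression models will be used to determine if any of baseline study variables modulate these effects on the outcome variables". The outcomes listed there are changes (BMI, lipids, blood pressure, HbA1c, VO2max, sedentary behaviour).

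One threshold of 0.05 covers all of these, and the paired tests are not marked as descriptive. The abstract (Methods/design) says what is compared: "Cardiometabolic risk biomarkers and changes in these variables will be compared between the intervention group and the control group at the four time points". The Measures section sets visits at baseline, 3, 6 and 12 months, so the baseline value of each outcome is due to be recorded. The section on study design and selection says that randomisation is by business unit.

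**The concern.** The stated test of the intervention is an analysis of variance, or a rank equivalent, of levels and of changes. A level comparison leaves the baseline out. A change-score comparison uses it, but fixes its slope at 1 whatever the true correlation. In large samples, and for any correlation between 0 and 1, neither is more precise than a comparison adjusted for the outcome's own baseline. Each also carries part of any chance baseline difference into the estimate.

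The paired tests raise a separate problem. Anything that moves both arms can make one or both significant. The protocol contains such a mechanism: under Blood pressure, "The undiagnosed participants will be advised to seek medical attention", with similar advice for cholesterol and glucose under Blood samples. That advice is not specific to an arm. Regression to the mean after a high first reading acts in both arms too. What is at stake is precision in the real comparison, and the chance that a significant within-arm change is read as benefit.

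**Working it through.** **The plan's own figure.** The article claims more than 90% power with at least 60 per group for sedentary behaviour. It gives no difference, SD or drop-out rate, so the claim can be neither confirmed nor refuted. Solving backwards (normal approximation, two-sided 0.05, independent participants): d = (1.960 + 1.282) × √(2/60) = 0.592 SD. With 60 per arm, power is 90% at d = 0.592, 0.78 at d = 0.5 and 0.59 at d = 0.4.

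**Inputs.** Two arms of 60 (article). The baseline to follow-up correlation r is not given, so 0.3 to 0.9 is assumed. Baseline and follow-up SDs are taken as equal and scaled to 1. One follow-up visit, clustering ignored.

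**Variance of the arm effect, relative to the follow-up level.** Level = 1; change = 2(1−r); baseline-adjusted = 1−r². Adjusted over change is (1−r²)/[2(1−r)] = (1+r)/2, a reduction of (1−r)/2. Against level the reduction is r².

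| r | Level | Change | Adjusted | Reduction vs change | Reduction vs level |
|---|---|---|---|---|---|
| 0.3 | 1 | 1.40 | 0.91 | 35% | 9% |
| 0.5 | 1 | 1.00 | 0.75 | 25% | 25% |
| 0.7 | 1 | 0.60 | 0.51 | 15% | 49% |
| 0.8 | 1 | 0.40 | 0.36 | 10% | 64% |
| 0.9 | 1 | 0.20 | 0.19 | 5% | 81% |

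Below r = 0.5, change scores are less precise than levels.

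**In power terms.** With 60 per arm and an assumed d = 0.5 (level / change / adjusted): r = 0.3 gives 0.78 / 0.64 / 0.82; r = 0.5 gives 0.78 / 0.78 / 0.89; r = 0.7 gives 0.78 / 0.94 / 0.97.

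**Chance imbalance.** Let the arms differ by D at baseline and the true effect be δ. Given D, the level comparison estimates δ + rD, the change comparison δ − (1−r)D, and the adjusted comparison δ. At r = 0.5 the first two are each off by half of D, in opposite directions.

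**Paired tests.** Suppose both arms have the same true change, so there is no intervention effect, and each paired test has power p. With independent arms, exactly one is significant with probability 2p(1−p).

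- p = 0.50: 2 × 0.50 × 0.50 = 0.50; only the intervention arm, 0.25.
- p = 0.80: 2 × 0.80 × 0.20 = 0.32; only the intervention arm, 0.16.

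A case that gives p close to 0.50: shared drift 0.2 SD, r = 0.7, 60 per arm. The standardised change is 0.2/√(2 × 0.3) = 0.258, and the noncentral t gives power 0.503. Drift and r are assumptions. Since 2p(1−p) peaks at p = 0.50, 50% is the maximum.

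**Clustering.** With 20 per business unit and ICC 0.05 (both assumed), the design effect is 1 + 19 × 0.05 = 1.95. Power at d = 0.592 falls from 0.90 to 0.64, and adjustment at r = 0.5, with the same design effect, restores it only to 0.76. Baseline adjustment therefore does not replace an analysis that accounts for units.

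**The case against.** The strongest reply is the regression sentence. A regression of change on arm plus the outcome's baseline gives the same arm effect as ANCOVA, so the adjusted estimate may be within what the authors intend. But the stated purpose is to learn which baseline variables modulate the effects. The arm contrast is assigned to analysis of variance, and the outcome's own baseline is not named as a covariate. The sentence narrows the point without removing it.

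Other replies stand and limit the claim:

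- A reader might infer that the plan ignores the baseline. Change scores do use it, only inefficiently.
- A reader might infer separate tests at each visit that lose everyone who misses that visit. The form of the analysis of variance is not stated, a repeated-measures form is not excluded, and missing-visit handling may sit in an unseen SAP.
- A reader might infer that the trial is short of power, or that few randomised units make imbalance likely. The power claim cannot be checked, and the number of business units is not given.
- Over repeated randomisations the unadjusted comparisons are not biased by imbalance. The bias is conditional on the imbalance observed, and the main issue is precision.
- The article lists the between-group comparison separately. It does not say that paired tests will be read as the intervention effect.
- For a stable measure such as BMI, r may be high and the gain over change scores small.

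**Conclusion.** The point holds as one of efficiency and clarity. The published text assigns the arm comparison to an unadjusted method, although a better one needs no data beyond those planned. The reduction in variance is 5% to 35% against change scores for r from 0.9 down to 0.3, and 9% to 49% against levels for r from 0.3 to 0.7. These figures rest on an assumed r, equal SDs, large samples and independent participants. Under randomisation by business unit they need not hold exactly. Adjustment also removes the conditional bias from a chance baseline difference.

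The paired tests give no evidence on the intervention. If both arms truly change alike and within-arm power is 50% to 80%, a discordant pair of results appears in 50% to 32% of trials, and half of those favour the intervention arm. The documents do not support the stronger conclusions that the trial is underpowered or that its planned comparison is biased on average.

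**What to change.** In the Data analysis section, define the treatment effect for each outcome as the between-arm difference with 95% CI from one model of the 3-, 6- and 12-month values. The terms are arm, visit, arm × visit and the baseline value of that outcome. The model should account for business unit, with a small-sample correction if units are few, because uncorrected standard errors from a random-effect model are then unreliable. Keep the regression on effect modulation as a separate, secondary analysis. Report within-arm changes descriptively, without p-values.

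The cost is analysis wording only. All the values required are already scheduled for collection, so no visit, measurement or participant is added.

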## Methods

### Study design, setting, participants and selection

This study will use a mixed-methods study design. Phase 1 of the study is a 12-month single-blind randomised controlled trial (RCT). Phase 2 will explore participant perceptions of the effectiveness of the intervention in the workplace.

In the first phase, the study participants will be assigned to an intervention group for 12 months or a control group. They will be randomised into one of two groups: (1) the combined standing desk–healthy messages group or (2) the control group.

The randomisation will be conducted by a qualified biostatistician independent from the core research team.

The potential for contamination will be minimised by adhering to various evidence-based approaches (Magill et al. 2019): (1) participants will be randomised by business unit, (2) participants will be requested not to share details of the intervention, (3) researchers will be asked not to share details of the intervention and (4) a sufficient number of research assistants will be recruited, each allocated to a single business unit. The RCT will be single blinded so that the first and second authors (assessors) are blinded to the group allocation of the study participants.

All adult office workers (18–65 years) from a specific credit and information management company based in Johannesburg (South Africa), working at least 50% of the workday at their desk, 5 days per week, will be invited to participate by the human resources analyst concerned with employee health and wellness through email and telephonic invitations. The inclusion criteria include access to telephone or mobile, email and/or internet and a desk or workstation within the setting; the ability to communicate in English; and the ability to walk or stand for at least 10 min. The exclusion criteria include participants who are pregnant, non-ambulatory or have a diagnosed medical or chronic condition that affects their ability to stand for 10 min or more. Furthermore, participants with other contraindications for working in the standing position and participants not working at the study site will also be excluded from the study. The total current staff complement of the company is 300, and all employees are housed in the same building. The building has three floors, with each respective floor subdivided securely by business unit, thus restricting the movements of staff in the setting.

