The sample size for phase 1 of the study will be determined based on the available resources and the assumption that at least 60 participants per group, adjusted for drop-out, will provide > 90% power to detect a significant difference (*p* < 0.05) in sedentary behaviour between the groups (O’Connell et al. 2015).

For phase 2, semi-structured focus group discussions, conducted by author 1, author 2 and research assistants, are planned with six groups of participants selected by participation in the intervention; each group will have six to eight participants. The principle of saturation in its purest sense (as in grounded theory methodology) will not be applied (Creswell 2007). However, the authors will apply the principle of saturation in the sense that it is anticipated that the sample size will be adequate to provide sufficiently rich data, and that a greater sample size would not yield a significant amount of new information (Tracy 2010).

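### If whole business units are allocated, the planned ANOVA and linear regression ignore unit, so standard errors are too small and the type I error exceeds 5%

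*Protocol article*

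**What the plan says.** All references are to the protocol article.

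- **Allocation** (Study design, setting, participants and selection). A general sentence says of the participants: "They will be randomised into one of two groups". The list of measures against contamination then opens with "participants will be randomised by business unit" and ends with "a sufficient number of research assistants will be recruited, each allocated to a single business unit". The building is described as having "each respective floor subdivided securely by business unit, thus restricting the movements of staff in the setting".
- **Sample size** (same section). The assumption is that "at least 60 participants per group, adjusted for drop-out, will provide > 90% power" for a difference in sedentary behaviour at p < 0.05. Participants are counted, and units are not.
- **Analysis** (Data analysis). "Comparison between groups will be made using analysis of variance or the non-parametric equivalent". Within-group changes use paired t-tests or rank equivalents. Multivariable linear regression examines whether baseline variables modify the changes in BMI, lipids, blood pressure, HbA1c, VO2max and sedentary behaviour. The significance level is 0.05.

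Nowhere does the article mention clusters, an ICC, a design effect, a random effect, cluster-robust standard errors or a unit-level analysis.

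**The concern.** Allocation by unit limits contamination only if everyone in a unit goes to the same arm. Randomising individuals within a unit would seat desk users beside controls. On the natural reading this is therefore a cluster-randomised trial, and the independent replicates for the treatment comparison are the units.

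The article itself gives reasons to expect correlation within a unit. Its members share a secured part of a floor and one research assistant. In the intervention group, assistants visit weekly to check the set-up, monitor use and encourage standing (Intervention section). With one assistant per unit, assistant and unit effects cannot be separated.

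ANOVA, its rank equivalent and ordinary linear regression all assume independent observations. Pairing in the within-group t-tests deals with repeated measurements on a person, not with the unit. At stake is every between-group claim: a chance difference between a few units could be reported as an effect of the desks and messages, with a confidence interval that is too narrow.

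**Working it through.** **1. The plan's own figure.** The power above 90% cannot be reproduced, because the article gives no effect size, standard deviation or drop-out rate. It can be solved backwards. With 60 independent participants per arm and two-sided α = 0.05 (sidedness is not stated), the standardised difference detectable with 90% power is

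d = (1.960 + 1.282) × √(2/60) = 0.592.

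At d = 0.5 the power is 78%, and at d = 0.6 it is 91%. The stated power therefore needs d of about 0.6 or more, and no clustering.

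**2. Inputs for the type I error.** From the article: 60 per group, so 120 in total, and α = 0.05. Assumed, because not given: equal unit sizes; 6 or 12 units in total; ICC of 0.01, 0.05 or 0.10 for the outcome as analysed.

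**3. Formulas.** With m participants per unit, the design effect is DE = 1 + (m − 1) × ICC. The naive standard error is too small by a factor √DE, so

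true type I error = 2 × [1 − Φ(1.96/√DE)].

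A simulation of the individual-level t-test (the same as a two-group ANOVA), with 20,000 trials per scenario, checks the formula.

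| Units in total | m | ICC | DE | Error, formula | Error, simulated |
|---|---|---|---|---|---|
| 12 | 10 | 0.01 | 1.09 | 6.0% | 5.8% |
| 12 | 10 | 0.05 | 1.45 | 10.4% | 10.0% |
| 12 | 10 | 0.10 | 1.90 | 15.5% | 15.7% |
| 6 | 20 | 0.01 | 1.19 | 7.2% | 7.1% |
| 6 | 20 | 0.05 | 1.95 | 16.0% | 16.4% |
| 6 | 20 | 0.10 | 2.90 | 25.0% | 25.5% |

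Worked line, 6 units at ICC 0.05: DE = 1 + 19 × 0.05 = 1.95; 1.96/√1.95 = 1.404; 2 × [1 − Φ(1.404)] = 0.160.

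With 20 units in total (m = 6) the formula still gives 5.6% to 11.0% over the same ICC range.

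**4. Power once clustering is respected.** Take d = 0.592, which has exactly 90% power under independence, and ICC = 0.05.

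- 3 units per arm: effective n per arm = 60/1.95 = 30.8. Power is 64% by the normal approximation and 43% with a cluster-level t-test on 2 × 3 − 2 = 4 degrees of freedom.
- 6 units per arm: effective n per arm = 60/1.45 = 41.4. Power is 77% and 68% (10 degrees of freedom).

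**5. The other reading.** If individuals were randomised within units, the treatment comparison would be free of between-unit variance. The naive test would then overstate the variance, with true-to-assumed ratio 1 − ICC. Its true error is 2 × [1 − Φ(1.96/√(1 − ICC))] = 4.9%, 4.4% and 3.9% at ICC 0.01, 0.05 and 0.10.

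**6. Limit of a unit-level permutation test.** With 3 units per arm there are C(6,3) = 20 allocations, so the smallest two-sided p is 2/20 = 0.10. With 4 per arm there are C(8,4) = 70, and the smallest p is 2/70 = 0.029.

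**The case against.** The strongest objection is that the wording on allocation is not decisive. The general sentence and the sample size both speak of participants, and randomising by unit could mean stratifying by unit. On that reading the naive test is slightly conservative (step 5), the opposite of the problem described. This stands as a condition on the conclusion. It does not rescue the plan: stratified allocation within units would not serve the contamination purpose given for it, and unit would still belong in the model.

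A second objection is that the size is assumed. That also stands. The listed regression outcomes are changes from baseline, and stable similarities between colleagues partly cancel in a change, so ICCs near or below the bottom of the range are plausible. A reader might take the highest figures as the expected error; the article supports no particular value.

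A reader might also add a shared manager, salary band or type of work as causes of clustering. The article does not say that a unit shares these. Salary band is only an individual questionnaire item. The shared space and assistant are enough for the point.

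Finally, a statistical analysis plan or full protocol that is not shown might handle clustering. But the article does not leave the method open. It names specific tests, and they do not match the allocation it describes.

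**Conclusion.** The point holds, conditional on whole-unit allocation, which is what the contamination rationale implies. Any positive ICC then puts the type I error of the planned between-group test above 5%. With 120 participants, equal unit sizes and an assumed ICC of 0.01 to 0.10, it is about 6% to 16% with 12 units and 7% to 25% with 6. The inflation is small with many units and a low ICC, and disappears only at ICC = 0.

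The documents do not support the unconditional statement that the standard errors are too small, because stratification within units is not strictly excluded. Either way, the allocation and analysis sections need to be reconciled before the data are analysed.

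**What to change.** 1. State explicitly that the unit of allocation is the business unit, and give the number of units per arm.
2. Replace the between-group ANOVA and the regressions with a linear mixed model that has a random intercept for business unit and a small-sample degrees-of-freedom correction such as Kenward-Roger. A cluster-level t-test is an acceptable alternative.
3. For non-normal outcomes, replace the rank test with a unit-level permutation test only if there are at least 4 units per arm. With 3 per arm it can never reach 0.05.
4. Restate the power with a design effect over a stated range of ICCs.
5. If stratification within units was meant, say so, include unit as a stratification factor, and reconcile this with the contamination rationale.

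Cost: the analysis change should need no new measurements, since allocation records should show each participant's unit. It is more than a change of wording, though. Confidence intervals become wider, and the power above 90% may no longer be attainable with 60 per group (step 4).
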